#### Data handling

Investigators will enter the collected data required by the protocol into the case report forms. Non-obvious errors or omissions will be recorded on data query forms, which will be returned to the researchers’ workshop for resolution. The data from all centers will be pooled and summarized with respect to demographic baseline characteristics, effectiveness, and safety observations.

#### Patient safety

Any adverse experiences (known as unfavorable or unintended signs, symptoms, or diseases occurring after treatment) related to EA treatment will be monitored. The research team will review all trial protocols, monitor participant safety, and investigate any adverse events. The trials will be terminated if there are concerns about patient safety.

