**Safety**					
Adverse events		**×**	**×**	**×**	**×**

EA, electroacupuncture; PUHTP, proportion of ulcers healed within trial period; VAS, visual analogue scale; WSA, wound surface area; the symbol ‘x’ is used as a check mark.

This trial will include an 8-week treatment period and a 1-month follow-up period. After randomization, patients will receive a total of 40 session treatments over a period of 8 weeks. Outcome measurements will be assessed at baseline (1 week after participants are diagnosed with pressure ulcer), as well as at the end of the fourth week and 8 weeks after randomization, and 1 month after conclusion of the treatment phase. Patients will be informed that they may be assigned to an EA group, or control group.

This trial will be carried out according to the principles of the Declaration of Helsinki (version Seoul, 2008). This study protocol has been approved by the ethical review boards of the Second Affiliated Hospital of Heilongjiang University of Chinese Medicine, with permission number LLP2011012. All participants will be asked to provide written informed consent before enrollment, and will be given sufficient time to reach a decision to participate and sign the consent form.

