### Blinding

The researchers are in charge of sending randomization information and also receiving notices of the patient’s assignation. It is not practical to blind the researchers to treatment allocations. In addition, it is not possible to prevent participants from knowing if they have received EA treatment or standard wound care. However, it is feasible to blind outcome assessors and statisticians.

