### Intervention

The intervention was designed according to the record in the ancient book of *Yellow Emperor’s Inner Bible,* in Chapter *Lingshu*-*Guanzhen*[16] and according to the recent study of acupuncture as a treatment for pressure ulcers [17]. Standard wound care is a non-EA therapy option in this trial. The EA protocol was developed in consensus with acupuncturists and experts, who are good at acupuncture. In addition, this protocol is consistent with the Standards for Reporting Interventions in Clinical Trials of Acupuncture (STRICTA) guidelines for the performance of EA studies [18].

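### The Patient safety section ties adverse-event monitoring to EA-related events, which no control participant can have, and conflicts with its own next sentence and with Table 1

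*Protocol article*

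**What the plan says.** Four statements in the protocol article bear on which adverse events are collected.

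- **Patient safety, first sentence:** "Any adverse experiences (known as unfavorable or unintended signs, symptoms, or diseases occurring after treatment) related to EA treatment will be monitored". The parenthesis defines an adverse experience broadly; the words after it narrow the definition by cause.
- **Patient safety, second sentence:** the research team will "monitor participant safety, and investigate any adverse events", with no limit by arm or cause.
- **Table 1, Safety block:** a row labelled "Adverse events" is marked at 0, 4 and 8 weeks and at 1 month after treatment, again with no limit by arm or cause.
- **Data handling:** the data will be "pooled and summarized with respect to demographic baseline characteristics, effectiveness, and safety observations". No relatedness filter is given, and no summary by arm is stated.

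The Intervention section describes the comparator thus: "Standard wound care is a non-EA therapy option in this trial". The Blinding section says that blinding the researchers is impractical and that "it is not possible to prevent participants from knowing if they have received EA treatment or standard wound care"; outcome assessors and statisticians can be blinded.

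**The concern.** The first sentence makes a causal link to EA part of the definition of what is monitored. An arm without EA cannot satisfy it. If site staff work to that sentence, a wound infection in a control participant has no reason to be recorded, while the same infection in an EA participant is recorded if someone attributes it to EA.

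This matters more here than in many trials. The intervention places a needle in the centre of an open wound at five sessions per week for 8 weeks, which is 40 sessions. The Background section itself lists pain and infection among the consequences of open ulcers, so such events can be expected without EA, and a control rate is what separates background from harm. Attribution made with allocation known can err either way: a real excess may be put down to the ulcer, or background events may be put down to the needle. The study is also a pilot meant to inform a larger trial, so its safety data will be carried forward.

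**Working it through.** The plan gives no adverse-event rate, so there is no figure of its own to reproduce. The check is mainly a comparison of texts.

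**Step 1. Can a control event qualify?** Under the first Patient safety sentence, an event must be related to EA. Control participants get standard wound care alone (Table 1 and the Control group section). Under that sentence, no control event qualifies.

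**Step 2. Do the other statements agree?**

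| Statement | Limited by cause? | Limited by arm? |
|---|---|---|
| Patient safety, first sentence | Yes, EA-related | In effect yes |
| Patient safety, second sentence | No | No |
| Table 1, Safety row | No | No |
| Data handling, safety summary | No | No |

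One statement is narrow and three are broad. The narrow one is the only one that defines which experiences are monitored. The others give a duty to investigate, a visit schedule and a summary. They conflict with the narrow sentence but do not state a capture rule to replace it.

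**Step 3. What would the difference look like?** This is illustration only. The assumptions are an all-cause proportion p of participants with an event, equal in both arms, and a share f of EA-arm events attributed to EA. With n = 18 per arm (Sample size section):

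- Full recording, expected per arm: 18 × p
- Narrow sentence, EA arm: 18 × p × f
- Narrow sentence, control arm: 0
- Chance of at least one recorded control event under full recording: 1 − (1 − p)^18

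| Assumed p | Full recording, each arm | Narrow, EA arm (f = 25% to 100%) | Narrow, control arm |
|---|---|---|---|
| 10% | 1.8 | 0.45 to 1.8 | 0 |
| 20% | 3.6 | 0.9 to 3.6 | 0 |
| 50% | 9.0 | 2.25 to 9.0 | 0 |

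The chance of at least one control event under full recording is 1 − 0.9^18 = 85% at p = 10%, and 1 − 0.8^18 = 98% at p = 20%. Under the narrow sentence it is zero at any p. Two arms with identical true rates would therefore look different whenever any EA-arm event was attributed to EA.

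**Step 4. What is collected in both arms regardless?** Table 1 schedules wound surface area (WSA) and pain on the visual analogue scale (VAS) at the same four time points in the trial as a whole, and WSA is traced and measured by blinded assessors. Enlargement of the ulcer and pain are therefore compared whatever happens to adverse-event capture. The Quality control section also documents reasons for withdrawal without restriction by arm. The exposed events are those that no outcome measures, such as wound infection and bleeding.

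**The case against.** A reader might infer that only EA-related events will be recorded, that the control arm therefore has none by definition, and that the arms cannot be compared for safety. The documents do not support that. The article does not say that other events go unrecorded; the very next sentence covers any adverse event, and Table 1 and Data handling carry no filter. This part of the objection stands: the defect is an inconsistency, and the forced zero follows only if the narrow sentence governs.

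Further points also stand. Ulcer enlargement and pain have a control comparison through WSA and VAS. The article does not say who judges relatedness, or that it is judged before an event is recorded, so an unblinded gatekeeper is a risk under the narrow reading and not a stated procedure. Termination is tied to safety concerns in general, not to EA-related events. Upper bounds on a rate after zero events in a small arm would reflect the number of participants and not the filter, so they do not measure this problem.

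It can also be said that a journal article leaves form content and event definitions to the full protocol. That is fair for lists of solicited events or question wording. It does not cover a rule that is stated and conflicts with other text on the page.

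**Conclusion.** The concern holds as an internal contradiction with a real consequence under one of its two readings. The first Patient safety sentence sets a criterion that no control participant can meet, and it disagrees with the sentence after it and with Table 1. If staff follow it, events such as infection and bleeding have no control-arm rate (0 of 18 recorded, whatever the truth), and EA-arm capture rests on attribution in a trial where allocation is known to researchers and participants. If they follow Table 1, the problem does not arise.

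The article gives no event rates, so the counts above rest on assumed values, and it does not show which reading the case report form adopts. The type I error rate, power, sample size and the efficacy comparison are unaffected. The importance is moderate: it should be corrected, and soon, because the Trial status section reports that recruitment is under way and events not recorded may not be recoverable.

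**What to change.** Reconcile the passages. In the Patient safety section, remove the link to EA as a condition for capture, that is, the qualifier in "related to EA treatment will be monitored". State instead that all adverse events in both groups are recorded in the same way at the visits already in Table 1, through the 1-month follow-up; that relatedness to EA is recorded as a separate attribute of each event; and that events are summarized by arm. Add the by-arm summary to Data handling so that it matches.

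The cost is a change of wording in the protocol and, if needed, the case report form, plus a little time at existing visits. No visit is added. The small downside is more events to record, most of them probably background to the ulcer; the by-arm summary puts them in context.

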#### Quality control

All staff will be required to undergo special training, including patient selection and exclusion, completing the case report form, and acupuncture method, before participating in the trial. Monitors will check case report forms and EA operation at the participating hospital once a month. Drop-outs and withdrawals (and the reasons) from the study will be fully documented throughout the treatment and follow-up periods.

### Ethics

Written informed consent will be obtained from each participant. This study is approved by the ethical review boards of the Second Affiliated Hospital of Heilongjiang University of Traditional Chinese Medicine.

## Discussion

Pressure ulcers remain a major public health problem. The results of this study will determine if EA is an effective intervention for patients with pressure ulcers. The results will also identify whether this therapy focuses on symptomatic relief.

Acupuncture, a kind of TCM, has been a form of healthcare in China for thousands of years. It has been reported to be of some benefit to patients with pressure ulcers, and could also enhance some of their signs and symptoms.

Currently, there are no randomized controlled trials (RCTs) about EA treatment for patients with pressure ulcers; therefore, we designed this study. This study aims to conduct a pilot study for a full-scale trial of EA for pressure ulcers, and to examine its potential effect in terms of pressure ulcers of future episodes. In addition, it also provides the feasibility of a larger clinical trial. The data pooled will shed new light on acupuncture, especially for EA intervention for pressure ulcers.

## Trial status

The trial is currently recruiting participants.

## Abbreviations

ChiCTR: Chinese clinical trial register; EA: Electroacupuncture; EPUAP: European pressure ulcer advisory panel; GCP: Good clinical practice; ITT: Intention-to-treat; NPUAP: National pressure ulcer advisory panel; PUHTP: Proportion of ulcers healed within trial period; RCT: Randomized controlled trial; STRICTA: Standards for reporting interventions in clinical trials of acupuncture; TCM: Traditional Chinese medicine; VAS: Visual analogue scale; WSA: Wound surface area.
